### Intervention

The 7-day residential program will begin on a Sunday and finish on a Saturday (see Table 1).

**Table 1 Tab1:** **Timetable of the program for carers**

	Morning	Afternoon	Evening
Sunday		• Welcome and orientation	Socialising
Monday	• Combating isolation	• Medical aspects of dementia	Socialising
		• Relaxation	
Tuesday	• Fitness	• Communication	Socialising
	• Reminiscence and reality orientation	• Assertion	
Wednesday	• Re-roling	• Therapeutic use of activities	Socialising
	• Nutrition	• Work simplification, organisation and safety at home	
Thursday	• Nursing skills	• Planning for the future	Carers’ outing
		• Using community services	
Friday	• Caring for self	• *Carers’ choice of topic*	Socialising
	• Relaxation		
Saturday	• Farewell		

#### Program for carers

There will be 14 intensive psychoeducation sessions for carers. These sessions will be delivered in an informal structure, with didactic segments, group work, modelling and role play. The sessions cover the following topics:*Combating isolation*. Carers will be encouraged to share their experiences of the caring role to establish an open, supportive relationship among carers.*Medical aspects of dementia*. This session will provide information on the causes of different types of dementia, behavioural and psychiatric changes that may occur, and other common comorbidities including depression and delirium.*Planning for the future*. The need to plan for future emergencies and unforseen events (e.g., unplanned hospitalisation or death of the carer) will be discussed in this session. Other issues such as driving, legal and financial matters, as well as Advance Care Planning will also be explored.*Re-roling*. This session will explore the issues pertaining to the changes in roles and responsibilities between the person with dementia and the carer. Practical problem solving skills will be taught to help carers encourage the person with dementia to allow the carer to take over some of the tasks while maintaining his/her dignity and to develop the carer’s confidence in taking over these roles.*Reminiscence and reality orientation*. Carers will be provided with information on techniques of reminiscence (e.g. use of a life history book), environmental reality orientation (e.g. use of signs or clocks) and validation to enable the person with dementia to maintain connection with their environment as well as improve the communication between the carer and the person with dementia.*Communication*. Information on receptive and expressive dysphasia that the person with dementia may experience and how these may affect communication will be provided, and then carers will have the opportunity to learn communication strategies to enhance understanding.*Assertion*. Carers will be provided with an understanding of assertive, non-assertive and aggressive behaviours, a “carer’s bill of rights” and strategies to cope with criticisms to ensure that they are heard and understood and their personal rights are maintained.*Therapeutic use of activities*. Activities that may be meaningful and enjoyable to the person with dementia will be identified in this session and carers will be provided with knowledge of activity analysis that enables them to break down familiar tasks into component steps and to modify or eliminate steps that prevent the person with dementia from completing them.*Work simplification, organisation and safety in the home*. Problem solving skills of prioritising, simplifying and using outside assistance will be explored to help carers achieve a balance of work, leisure and rest in their daily life. Tools to identify risks within the home environment will be provided and safety measures to minimise the risk to the person with dementia will be discussed.*Nursing skills*. Clinical issues associated with dementia such as incontinence, medication, mobility, personal care and acute illness will be covered and carers will receive hands-on experience in using clinical care equipment that can be used to aid care practices.*Fitness*. Information about the benefits of exercise for both the person with dementia and the carer will be provided, and a daily exercise routine will be established.*Nutrition*. Changes in diet, food intake and nutritional needs of the person with dementia will be examined, and carers will be provided with practical skills to enhance intake as well as improve the eating experience.*Caring for self*. This session will provide carers with the opportunity to identify their need for support and they will be taught a variety of relaxation and stress management techniques.*Using community services*. Information about the types of support services available in the community as well as how to contact and access these services will be provided.

#### Program for people with dementia

The program for people with dementia will include activities that focus on sensory stimulation, environmental orientation, brain training, physical activity, reminiscence, self-expression, creativity, social interactions and relaxation. Outings may be arranged depending on personal preferences. A large variety of activities will be arranged to cater to different personal preferences and individual needs. The people with dementia will also be provided with the opportunity to discuss changes in their memory and their brain on a physiological level depending on their ability and willingness to receive the information.

### Assessment

Global cognitive function of people with dementia will be assessed at baseline by RACF staff using the Mini Mental State Examination (MMSE) (Folstein et al. 1975).

Outcome and additional measures will be collected at all three time points: baseline, post 1 and post 2. Information will be collected through self-report and proxy questionnaires, as well as through interviews with the carer.

#### Outcome measures

The primary outcome is carer psychological distress measured using the 10-item Kessler Psychological Distress Scale (K-10) (Kessler et al. 2002). The K-10 is a self-report measure of global psychological distress based on questions about anxiety and depressive symptoms; higher scores indicate greater distress. The version used in this study employs a referent time frame of ‘the last four weeks’ instead of ‘the last 30 days’ in the original questionnaire (ABS 2003).

Secondary outcomes are carer burden, carer quality of life, time to residential care placement, carer functional health status, carer needs, resource utilisation, person with dementia instrumental activities of daily living, person with dementia activities of daily living, person with dementia quality of life, person with dementia neuropsychiatric symptoms, person with dementia agitation and dementia severity.

*Carer burden*: The 12-item Zarit Burden Interview, short version (ZBI-12) (Bédard et al. 2001; Zarit et al. 1980) is a self-report measure of burden experienced in the caring role. The ZBI-12 has been shown to yield results comparable to those of the original full version (Bédard et al. 2001). Higher scores indicate greater burden.*Carer quality of life*: The 13-item Older People’s Quality of Life Questionnaire – Brief (OPQoL-Brief) (Bowling et al. 2013) will be used to measure quality of life. Higher scores indicate better quality of life.*Time to residential care placement*: Time between recruitment and residential care placement of the person with dementia will be measured in days.*Carer functional health status*: The 12-item Short Form Health Survey, version 2 (SF-12v2) (Ware et al. 1996) will be used to assess carers’ functional health status in the physical and mental domains; higher scores indicate better health.*Carer needs*: A 11-item self-report questionnaire (Harrison et al. 2013) covering various areas on which carers for people with dementia may need information will be used to assess the met and unmet needs of the carer.*Resource utilisation*: The Resource Utilization in Dementia – Lite instrument (RUD Lite) (Wimo and Winblad 2003) will be used to assess the utilisation of both formal and informal care and the associated costs. This is administered as an informant-report questionnaire rather than through an informant interview.*Instrumental activities of daily living (IADL)*: The Instrumental Activities of Daily Living Scale (IADL) (Lawton and Brody 1969) will be used to assess people with dementia’s competence in performing eight types of IADL. This will be administered in the form of an informant-report questionnaire.*Activities of daily living (ADL)*: The Physical Self-Maintenance Scale (PSMS) (Lawton and Brody 1969) will be used to assess people with dementia’s competence in six types of behaviours including toileting, feeding, dressing, grooming, physical ambulation and bathing. The version used here separates toileting into two items covering bladder and bowel control. This will be administered as an informant-report questionnaire.*Quality of life*: The proxy version of the 13-item Quality of Life – AD (QoL-AD) (Logsdon et al. 1999, 2002) will be used to assess the quality of life of people with dementia.*Neuropsychiatric symptoms*: The 12-item Neuropsychiatric Inventory (NPI) (Cummings et al. 1994) is an informant-rated measure of the severity and frequency of behavioural and psychiatric disturbances in the people with dementia, collected through an interview with the carer. Higher scores indicate more BPSD.*Agitation*: The 37-item Cohen-Mansfield Agitation Inventory – Community (CMAI-C) (Cohen-Mansfield et al. 1995) is an informant-rated measure of the frequency of agitated behaviours in the people with dementia, collected through an interview with the carer. Higher scores indicate greater agitation.*Dementia severity*: The Global Deterioration Scale (GDS) (Reisberg et al. 1982) will be used to classify people with dementia based on the relative severity of their cognitive impairment and their function in activities of daily living; higher scores indicate more severe dementia. This will be rated by the staff of the respite facility.

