The level of burden experienced by carers can be influenced by a myriad of factors. Behavioural and psychological symptoms of dementia (BPSD) (e.g., aggression, agitation) have been shown to be associated with carer burden (Black and Almeida 2004; Donaldson et al. 1998). Moreover, carers who reported lower satisfaction with the social support they receive or had greater reactions to the person with dementia’s behavioural problems had more symptoms of depression (Mittelman et al. 2008). The association between severity of the illness (either cognitive or functional impairment) and carer burden, however, was weak (Brodaty and Hadzi-Pavlovic 1990). Carer outcomes may also be influenced by the specific coping strategies used or the level of self-efficacy (Saad et al. 1995; Kneebone and Martin 2003; Fortinsky et al. 2002; Gilliam and Steffen 2006).

Adverse carer outcomes can lead to adverse outcomes in people with dementia. For instance, high levels of carer burden is a consistent significant predictor of institutionalisation (Yaffe et al. 2002; Gaugler et al. 2003; Hébert et al. 2001), and carer psychological morbidity was also a significant predictor of mortality of the care recipient (Brodaty et al. 1993). Therefore, carer interventions may benefit both the carer and the person with dementia. Carer interventions have significant but modest effects in improving carer knowledge, reducing carer burden, reducing psychological morbidity and delaying institutionalisation (Brodaty et al. 2003; Pinquart and Sörensen 2006). There is evidence that these effects can be maintained for up to 11 months post-intervention (Pinquart and Sörensen 2006). In particular, a 10-day Prince Henry Hospital residential carer training program proved effective in delaying residential care placement, delaying mortality, reducing carer’s psychological morbidity and lowering care costs (Brodaty and Gresham 1989; Brodaty and Peters 1991; Brodaty et al. 1993, 1997). These results suggest that carer training provided early in the course of dementia has significant benefits on the outcomes of people with dementia, and therefore such intensive carer training programs should be made more extensively available.

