Residential respite care is defined as alternative, short-term care in a residential aged care facility (RACF) with the main purpose of providing the family carer with respite and support. The use of residential respite care has steadily increased in Australia, but take up rates remain low, with only 32% of eligible people with dementia accessing residential respite care services within 12 months of gaining approval (AIHW 2012). There appears to be little empirical support for the efficacy of residential respite care, with some studies even reporting adverse effects on people with dementia, such as an increase in problem behaviours and earlier institutional placement (Brodaty and Gresham 1992). However, anecdotal reports from carers suggest residential respite care may have significant benefits provided carers are well informed and the most appropriate services are utilised. Residential respite care can provide an opportunity to combine existing knowledge about carer interventions with respite.

The principal aim of this study is to evaluate, in an open single-arm trial, the effects of the *Going to Stay at Home* program, which is adapted from the Prince Henry Hospital program for use with residential respite.

It is hypothesised that:carer psychological distress will be reduced at 6- and 12-month follow-up compared to baseline,carer burden will be reduced at 6- and 12-month follow-up compared to baseline,there will be no increase in BPSD in the person with dementia, anda minimum of 60% of carers will have the person with dementia still living at home at 12-month follow-up.

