### Statistical analysis

#### Sample size

A target sample size of 100 person with dementia-carer dyads has been estimated to provide over 80% power to detect a moderate effect size (Cohen’s d = 0.3) difference at a significance level of 0.05 (two-sided), assuming a medium within-subject correlation (ρ = 0.5) between pre- and post-intervention measures.

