#### Outcome analyses

The difference in outcome measures before and after intervention will be examined using a paired *t*-test at a significance level of 0.05 (two-sided). To control for covariates (NPI severity, dementia severity) linear mixed models will be used.

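### The before-after tests of burden and BPSD take no account of placement, so in this single-arm study any fall in burden after placement would be counted as a program effect

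*Protocol article*

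**What the plan says.** All references are to the protocol article.

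- **Background, hypotheses.** The second hypothesis is that "carer burden will be reduced at 6- and 12-month follow-up compared to baseline". The third is that BPSD will not increase. The fourth asks that a "minimum of 60% of carers will have the person with dementia still living at home at 12-month follow-up".
- **Study design and Assessment.** There is one arm. Outcome measures are collected at baseline, 6 months and 12 months, with no restriction by where the person with dementia lives.
- **Outcome measures.** The ZBI-12 is a "self-report measure of burden experienced in the caring role". The NPI and CMAI-C are rated through an interview with the carer. Time to residential care placement is a separate secondary outcome.
- **Outcome analyses.** "The difference in outcome measures before and after intervention will be examined using a paired" t-test. Linear mixed models are added to adjust for NPI severity and dementia severity. Placement is neither a covariate nor a stratum.
- **Missing data.** Patterns of missingness will be examined, and missing items handled as the literature on each instrument suggests. This does not cover scores that are observed but change meaning after placement.
- **Discussion.** The results are to show whether the program reduces distress and burden and delays institutionalisation.

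**The concern.** The ZBI-12 asks about the caring role, and placement changes or ends much of that role. The hypotheses themselves foresee that a sizeable minority of dyads may no longer be at home at 12 months. With no comparison group, a before-after mean cannot separate a program effect at home from relief that follows placement. A dyad that counts against the fourth hypothesis can therefore help to confirm the second.

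Placed dyads may also stop responding. The Background section says that "high levels of carer burden is a consistent significant predictor of institutionalisation", so those who leave are unlikely to be a random subset and the remaining pairs are selected.

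For BPSD, the setting and what the carer sees both change after placement, so scores before and after are not like for like.

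At stake is the reading of two named hypotheses, on secondary outcomes, in a study meant to inform policy. Nothing here concerns the primary outcome, the K-10.

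**Working it through.** **Inputs from the Sample size section.** "A target sample size of 100 person with dementia-carer dyads"; effect size d = 0.3; pre-post correlation 0.5; "difference at a significance level of 0.05 (two-sided"); power stated as over 80%.

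**Inputs from the hypotheses.** At least 60% at home at 12 months, so up to 100% - 60% = 40% not at home is compatible with the hypothesis.

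**Assumptions, not in the documents.** Baseline SD 1; no change in dyads at home; burden in placed carers falls by x SD, with x from 0.25 to 1.0; share placed p from 10% to 40%.

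**1. The plan's own figure.** The SD of change is sqrt(2(1 - 0.5)) = 1, so the standardised change is 0.3. With n = 100 the noncentrality is 0.3 × 10 = 3.0, and the noncentral t with 99 df gives power of 84.4%. The protocol's statement "estimated to provide over 80% power to detect a moderate effect size" is correct. The sample size is not the problem.

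**2. Placed carers respond and their burden falls.** The mean change over all dyads is -p·x. The variance of change is 1 + p(1 - p)x². The false rate is the chance that the two-sided 0.05 paired t-test is significant in the direction of reduction, nominally 2.5%.

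Example with p = 0.3 and x = 0.5: mean = -0.3 × 0.5 = -0.15; SD = sqrt(1 + 0.21 × 0.25) = 1.026; noncentrality = 10 × 0.15/1.026 = 1.46; false rate 30%.

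| Share placed | Relief x (SD) | Mean change (SD) | False finding of reduced burden |
|---|---|---|---|
| 10% | 1.0 | -0.10 | 16% |
| 20% | 0.5 | -0.10 | 16% |
| 20% | 1.0 | -0.20 | 45% |
| 30% | 0.25 | -0.075 | 11% |
| 30% | 0.5 | -0.15 | 30% |
| 30% | 0.8 | -0.24 | 61% |
| 40% | 0.25 | -0.10 | 16% |
| 40% | 0.5 | -0.20 | 49% |
| 40% | 0.75 | -0.30 | 80% |

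The smallest significant mean change at n = 100, with an SD of change of 1, is 1.984/10 = 0.198 SD. With 40% placed, the whole planned effect arises from placement alone when x = 0.3/0.4 = 0.75 SD. With 20% placed it would take 0.3/0.2 = 1.5 SD.

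**3. Placed dyads do not respond.** Suppose the 30% with the highest placement propensity leave, with no true change, and propensity has correlation r with burden at one visit. Among the 70 who stay, the mean at that visit shifts by -r × 0.348/0.70 = -0.497r, where 0.348 is the normal density at the 70th percentile. The mean at the other visit shifts by half of this, because the pre-post correlation is 0.5. The size of the spurious change is therefore 0.248r. Rates are from simulation with 20,000 replicates.

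| Placement follows | r = 0.3 | r = 0.5 | r = 1.0 | Direction of false findings |
|---|---|---|---|---|
| Follow-up burden | -0.07 SD | -0.12 SD | -0.25 SD | Reduced: about 9%, 18%, 58% |
| Baseline burden | +0.07 SD | +0.12 SD | +0.25 SD | Increased: about 9%, 18%, 58% |
| Both equally | 0.00 SD | 0.00 SD | 0.00 SD | Nominal, 2.5% each way |

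The sign depends on which burden drives placement. The documents do not say.

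**4. Cost of looking only at dyads at home.** With 60 dyads, the noncentrality is 0.3 × sqrt(60) = 2.32 and power for d = 0.3 is 63%.

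**The case against.** - **The size of relief is assumed.** This stands. The documents give no figure, and the Background section says that burden may persist for up to two years after admission to formal care. Relief could be near zero, in which case step 2 produces little or no bias. At 0.25 SD the false rate is still 11% to 16% with 30% to 40% placed.
- **40% is not a forecast.** This stands. It is the complement of a hypothesised minimum, neither an expected value nor a cap, and dyads not at home may include deaths. With 10% placed, even a fall of 1.0 SD gives 16%.
- **A reader might infer that dropout also favours the hypothesis.** The documents do not support this. They say that burden predicts institutionalisation, not at what time it was measured. If placement follows baseline burden, those who remain regress upward and the bias runs against the hypothesis.
- **A reader might infer that the BPSD hypothesis would be falsely confirmed too.** This is not supported either. The only direction the article gives comes from studies of residential respite, some of which reported more problem behaviours. That would work against the hypothesis.
- **The plan also has mixed models and an examination of missing-data patterns.** True, but neither names placement, and neither addresses observed scores from carers who are no longer caring at home.
- **Handling of events after baseline is commonly left to a fuller document.** That would answer a complaint about missing wording. Here the article fixes a before-after test and, in the same plan, foresees the event that changes what the test measures. The single arm leaves nothing to separate the two.

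**Conclusion.** The concern holds in a limited form. The stated comparison can show reduced burden with no benefit at home, because any relief after placement enters the mean change. With 30% placed and an assumed relief of 0.25 to 0.8 SD, this gives -0.08 to -0.24 SD and a false rate of about 11% to 61% against 2.5%. These figures rest on a normal model, the plan's correlation of 0.5, no change at home, and a placed share and relief that the documents do not supply.

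The bias from dropout has no fixed sign, and the direction for BPSD is unknown. It would be too strong to say that the plan must produce a false burden result, or that every route leads there. The sponsor should make the change. It affects what may be concluded on secondary outcomes that are named hypotheses, and not the sample size or the primary outcome.

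**What to change.** 1. Keep the all-dyad before-after comparison in Outcome analyses.
2. Beside it, report the ZBI-12, NPI and CMAI-C change at 6 and 12 months separately for dyads at home and dyads placed at that visit.
3. Show baseline scores for both groups, and for dyads lost through death or non-response, so that selection can be judged.
4. State in advance that a fall in burden will not be attributed to the program if it appears only when post-placement scores are included.

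A supportive rank analysis that gives placed dyads the worst change is optional. It should not be a condition for the burden claim, because it mixes burden with placement, which already has its own outcome.

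**Cost.** Analysis and reporting text only; time to placement is already collected. The at-home group is itself selected and smaller, with about 63% power for d = 0.3 if 60 dyads remain, so it should not replace the all-dyad test. The burden result may be less favourable.

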
### Interview and focus group

Carers will be asked to describe the effects of the program and which aspects they found most helpful. Focus groups will be held with managerial staff to discuss the impact of the program on facility-wide practices and the potential for similar programs to continue within the facility.

